#### Tertiary outcomes – Reduction of economic burden

##### Hypotheses

Vaccinated patients show lower healthcare utilisation, costs and sick-leave days than non-vaccinated patients.

##### Study population

*(The study population is identical to* secondary outcomes, section d.) 300,000 persons ≥60 years, living in Thuringia, who are insured in the AOK PLUS. The exposed cohort group is expected to consist of about 130,000 patients with pneumococcal and/or influenza vaccination in 2014; the unexposed cohort group are patients without pneumococcal vaccination in 2008–2017 and without influenza vaccination in 2012–2017. The observation period covers the years 2015 to 2017. We use real-world claims data to determine resource utilisation and costs across all sectors of medical care. A social health insurance (SHI) perspective is adopted. All routine data collected by health insurances are anonymous.

##### Outcome measures

Mean differences between exposed and unexposed persons in healthcare costs and resource utilisation including hospital care, rehabilitation, outpatient visits, medication, remedies, therapeutic aids, nursing care as well as sick-leave days, followed up at intervals of 1, 2 and 3 years.

##### Statistical analyses

Retrospective cohort study using adequate adjustment methods (multiple regression analysis, propensity score matching). The data for analysis will be complete; hence no particular missing data handling is necessary.

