*Hypothesis.* The incidences of influenza, pneumonia, IPD and sepsis are lower in people vaccinated than non-vaccinated over 60 years of age.*Study population.* To quantify the impact of influenza and pneumococcal vaccination on influenza, pneumonia, IPD and sepsis incidence and outcomes, a retrospective database study will be performed including about 300,000 persons ≥60 years, living in Thuringia, who are insured with one of the largest statutory health insurances in Germany (AOK PLUS, insured persons form about 40% of the Thuringian population). The exposed cohort group is expected to consist of about 130,000 patients with pneumococcal and/or influenza vaccination in 2014; the unexposed cohort group are patients without pneumococcal vaccination in 2008–2017 and without influenza vaccination in 2012–2017. The observation period covers the years from 2015 to 2017. The study is partly retrospective (2008–2016) and partly prospective (2017). The study was designed in 2017 and we have commenced in 2017 to acquire the data from 2008 to 2016 which are available from German SHIs with a regular delay of 9–12 months, so that the earliest time a SHI can transfer 2016 data is the end of 2017. Data preparation for statistical analysis has just begun and will not be finished before the end of 2018. As the inclusion of patients of 60 years and above in Thuringia insured with the SHI AOK PLUS practically corresponds to a complete survey, power calculations are not regarded as useful. All routine data collected by health insurances are anonymous.*Outcome measures.* Incidence rates and hospital/ICU admission rates of influenza, invasive pneumococcal diseases, pneumonia and sepsis, as well as in-hospital and long-term mortality will be compared between vaccinated and unvaccinated persons.*Statistical analyses.* Retrospective cohort study using adequate adjustment methods (multiple regression analysis, propensity score matching). The data for analysis will be complete; hence no particular missing data handling is necessary.
*Retrospective study based on health insurance claims data from Associations of Statutory Health Insurance Physicians (ASHIPs).*

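### Complete claims records are declared to need no missing-data handling, but they are not complete 1-, 2- and 3-year follow-up: leaving the insurer is uncovered and the role of death in the cost comparison is undefined

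*Protocol article*

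**What the plan says.** The sentence appears twice for this cohort in the protocol article: under Secondary outcomes, in the retrospective cohort study on health insurance claims data (study d), and under Tertiary outcomes, Statistical analyses. It reads: "The data for analysis will be complete; hence no particular missing data handling is necessary".

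The design around it is as follows.

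- **Population:** "300,000 persons ≥60 years, living in Thuringia, who are insured in the AOK PLUS". The exposed group is expected to be "about 130,000 patients with pneumococcal and/or influenza vaccination in 2014". The unexposed are those "without pneumococcal vaccination in 2008–2017 and without influenza vaccination in 2012–2017".
- **Time:** "The observation period covers the years 2015 to 2017".
- **Secondary outcomes (study d):** incidence rates and hospital and intensive-care admission rates, and "in-hospital and long-term mortality will be compared between vaccinated and unvaccinated persons".
- **Tertiary outcomes:** mean differences in cost, resource use and sick-leave days, "followed up at intervals of 1, 2 and 3 years".
- **Methods named:** multiple regression and propensity score matching.

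The Discussion acknowledges possible confounding by indication and a healthy-vaccinee effect, and offers covariate adjustment as the remedy.

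**The concern.** The sentence settles a question that the design leaves open. Claims data can be complete for every month a person is insured and still not cover that person for one, two or three years. Follow-up can stop early for two reasons, and they differ in kind.

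- **Death.** The plan expects it, because mortality is compared between the groups. From the insurer's perspective, which the tertiary analysis adopts, cost after death is truly zero and so is fully observed.
- **Leaving the insurer.** The source is one insurer with about 40% of the Thuringian population. A person who moves to another insurer still incurs costs, but the data no longer show them.

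Someone who follows the sentence literally has two obvious routes to a 3-year mean. One is to sum what is recorded for everyone, which sets leavers' later costs to zero. The other is to keep only people with three full years, which discards those who died and their end-of-life costs. Regression and propensity score matching address differences between the groups in measured covariates. They do not correct unequal observation time.

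At stake is the tertiary comparison of costs. Under the expected sizes there are 130,000 exposed and at most 300,000 − 130,000 = 170,000 unexposed. Random error will be small in groups of this size, so an artefact of a few per cent could be read as an effect.

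**Working it through.** The article gives no power figure, death rate or exit rate for this cohort, so there is no plan figure to reproduce. Every rate below is an assumption, used to show mechanism and scale.

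**Inputs from the article:** 300,000 persons; observation 2015–2017, so t = 3 years; cost horizons of 1, 2 and 3 years.

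**Step 1: how many lack three full years.** With annual exit q (death plus leaving), the share gone by year 3 is 1 − (1 − q)³.

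| Assumed q | Gone by year 3 | Of 300,000 |
|---|---|---|
| 1% | 3.0% | about 8,900 |
| 3% | 8.7% | about 26,200 |
| 5% | 14.3% | about 42,800 |
| 7% | 19.6% | about 58,700 |

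**Step 2: recorded costs summed for everyone.** Let cost be 1 unit per person-year in both groups, zero after death and unrecorded after leaving. With annual death d and leaving l, put r = (1 − d)(1 − l). Summing 36 months gives a recorded mean of (1/12)(1 − r³)/(1 − r^(1/12)). The true mean uses l = 0.

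Worked case, d = 4% in both groups, leaving 1% (vaccinated) and 3% (unvaccinated):

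- True, both groups: r = 0.96, mean 2.828.
- Vaccinated, recorded: r = 0.96 × 0.99 = 0.9504, mean 2.788.
- Unvaccinated, recorded: r = 0.96 × 0.97 = 0.9312, mean 2.709.
- True ratio 2.828/2.828 = 1.000; recorded ratio 2.788/2.709 = 1.029.

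Four settings together:

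| Death, vacc./unvacc. | Leaving, vacc./unvacc. | True ratio | Recorded ratio |
|---|---|---|---|
| 4% / 4% | 2% / 2% | 1.000 | 1.000 |
| 3% / 5% | none | 1.030 | 1.030 |
| 4% / 4% | 1% / 3% | 1.000 | 1.029 |
| 3% / 5% | 1% / 3% | 1.030 | 1.060 |

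The second row shows that death alone creates no gap between true and recorded accrued cost. The 1.030 is a real difference in cost accrued because one group lives longer, at equal cost per month alive. The third row is pure bias from leaving. In the first row the ratio is unaffected, but both means are understated (2.748 against 2.828, about 2.8%).

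**Step 3: only people with three full years.** Let a year in which a person dies cost 4 units and any other year 1 unit, with no leaving. The all-persons mean is (1 + 3q)[1 + (1 − q) + (1 − q)²], where q is now annual death.

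- Vaccinated, q = 3%: 1.09 × 2.9109 = 3.173.
- Unvaccinated, q = 5%: 1.15 × 2.8525 = 3.280.
- All-persons ratio: 3.173/3.280 = 0.967. Survivors-only ratio: 3/3 = 1.000.

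Under these assumptions a 3.3% lower cost among the vaccinated disappears once those who died are removed. At a death-year cost of 2 units the all-persons ratio is 1.001, so the loss depends on how costly the last year is.

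**The case against.** The strongest reply is that the sentence is about records. For the hospital discharge data the article calls the data complete apart from cases with unknown age or gender. For the pneumonia quality-assurance data it cites full documentation. For the surveys it discusses item non-response. On that reading, completeness means no empty fields. It does not forbid person-time or censoring, and those details can sit in a fuller plan. The article also proposes neither a survivors-only analysis nor a zero-cost rule for leavers.

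Much of this stands. Silence on enrolment windows or censoring would not be a finding in a condensed article. The article is not silent, however. It draws a conclusion, that no handling is needed, for a design whose 1-, 2- and 3-year horizons require some. Read as a remark about records, the sentence is true, but the conclusion does not follow.

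A reader might infer more than the article supports:

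- **That deaths bias the cost comparison.** For accrued insurer cost they do not (Step 2, second row). Whether accrued cost, cost per person-time or cost among survivors is wanted is a choice of estimand.
- **That leaving does differ by vaccination status.** The article does not mention leaving the insurer at all. It follows from the single-insurer source as a possibility, and its size and direction are unknown.
- **That longer survival of the vaccinated is hypothesised.** The stated hypotheses for this cohort concern incidence, utilisation, costs and sick-leave days. Mortality is only listed for comparison.
- **That incidence is biased or the cost result could reverse.** Incidence rates on person-time can absorb exits, and no expected cost effect is given against which a reversal could be judged.

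**Conclusion.** The point holds in limited form. The sentence claims a completeness that the follow-up does not have, and in the two claims-cohort sections it should not stand as written. Leaving the insurer is the part that leaves costs unobserved. Death needs a stated role in each outcome, but it is not missing data for accrued cost.

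The size cannot be derived from the article. Under the assumed 1% versus 3% annual leaving with equal 4% mortality, the 3-year cost ratio moves from 1.00 to about 1.03. With equal leaving the ratio does not move. Restricting to full follow-up can hide a difference of similar size (0.967 shown as 1.000), but only under the assumed 3% versus 5% mortality and a death year costing four times the usual.

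The unexposed definition, which runs to the end of 2017, conditions membership on events during follow-up. That is a related but separate problem and is not counted here. The same completeness sentence in the study of physicians' association claims (study e) is also outside this point, because that study takes yearly or seasonal proportions over an external denominator.

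**What to change.** Replace the sentence in both places (Secondary outcomes, study d; Tertiary outcomes, Statistical analyses) with text to this effect:

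- Records are complete for insured time.
- Incidence uses person-time, censored at death or at leaving the insurer.
- Mortality is analysed as time to event.
- Costs at 1, 2 and 3 years include all persons, with zero cost after death and mortality reported alongside.
- Leaving the insurer is treated as censoring, with a censoring-adjusted cost estimator. Inverse-probability-of-censoring weights are one option; other valid estimators would serve.
- Numbers leaving are reported by vaccination group and year.
- An analysis restricted to full follow-up is a sensitivity analysis only.

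The cost is a few lines of text and modest programming. It assumes that insurance start, end and death dates can be obtained from the insurer, which the article does not state. The article reports that data preparation had only just begun, so the change was feasible at that stage. If very few people left, the adjusted and unadjusted cost estimates will nearly agree, and reporting the counts will show that.

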## Discussion

This project is part of the trans-sectoral InfectControl2020 consortium, hosted by the Leibniz Institute for Natural Product Research and Infection Biology e. V. The consortium is concerned with the “rapidly increasing threat…arising from new or resistant pathogens….This threat is further afflicted by a drastic lack of (new) effective drugs as well as insufficient preventive and diagnostic possibilities” (http://www.infectcontrol.de/de/english.html). Vaccination is an effective measure to prevent infections and subsequently – by reducing the number of infections – also the use of antibiotics and severe consequences such as sepsis. Moreover, decreasing use of antibiotics can reduce the development and spread of antimicrobial resistance [68]. With this study we add to the consortium’s goals of finding new methods of infection-prevention by providing additional behavioural insights about vaccine hesitancy regarding influenza and pneumococcal vaccine in the elderly and about evidence-informed vaccination intervention design and evaluation.

The study offers unique learning opportunities for theory-based and evidence-informed intervention development and evaluation. Firstly, it uses a theoretical model of vaccine hesitancy to assess the underlying reasons for vaccine hesitancy that are addressed by the intervention. Using theory-based approaches has been shown to increase the success of interventions [69], however, in the field of vaccination advocacy there is a lack of theory-based interventions [70]. Additionally, this study also explicitly takes processes of cognitive ageing into account and applies a user-centred design approach. Secondly, triangulation and integration of diverse types and sources of data to target and evaluate the intervention will provide rich insights into the processes of behavioural change, user-centred design approaches as well as future promising principles of vaccine advocacy. Thirdly, the evaluation of the intervention on several levels (hesitancy, behaviour, disease and economic burden) allows for comparing and cross-validating results from different sources, which creates insights for future evaluation processes. It also allows identification of the challenges, benefits and pitfalls of the respective data sources (e.g., the national monitoring of disease incidences with data from health insurance refund claims is piloted and evaluated).

An additional goal of the intervention is to educate about sepsis as a severe consequence of infections. This is another innovative aspect of this project. WHO has recently recognised the importance of preventing sepsis by acknowledging a new resolution [21]. This study will show whether an increase in knowledge was obtained with the intervention and whether knowing more about sepsis decreases vaccine hesitancy and increases vaccination behaviour.

Moreover, the use of different data sources allows a pathogen-specific (influenza, invasive pneumococcal disease) and syndrome-specific (pneumonia, sepsis) evaluation of the reduction of vaccine-preventable diseases (secondary outcome).

Finally, the study expands real-world, data-based evidence on the relationship between vaccination uptake and clinical and economic burden of disease (influenza, pneumonia, IPD and sepsis).

Generalisability and adaptability of the specific intervention to other federal states in Germany will depend on how similar the target group’s characteristics and determinants of vaccination are to other federal states. Assuming similar reasons of vaccine hesitancy, the content of the intervention is suitable for other federal states, too. Assuming, on the contrary, that characteristics differ, such as reasons for vaccine hesitancy, lifestyle or values, specific distribution channels and visual key elements need to be adapted.

Due to the multi-methods and multi-data sources approach for intervention evaluation the results will be multifaceted, too. While this creates unique opportunities, it also comes with considerable challenges: data may sometimes be difficult to compare. Furthermore, limitations of the individual data sources are the following:Microbiological diagnostics of the secondary outcome pneumonia is not standardised between German hospitals.Although ALERTSNet aims to cover all of Thuringia, it only covers specific centres at certain times.ICD codes used by the German DRG statistics are considered to have high specificity, but only moderate sensitivity, thus being prone to an underestimation of disease prevalence, e.g., for sepsis by up to 3.5-fold [71, 72].Results from cohort studies assessing the impact of vaccination on disease incidences or resource utilisation might be subject to confounding by indication or healthy vaccinee bias. However, relevant covariates will be collected and adjusted analyses will be performed to mitigate this risk.Awareness for the intervention could be so low that stratifying data per material or source of information might be difficult. If awareness is below 50% in the first 100 participants of the representative study after wave one, participants with awareness for the intervention will be oversampled to reach a sample of at least *n* = 350 participants per group. Otherwise, reliable statistical analyses about the effects of the single aspects of the intervention will be not possible.

The intervention is limited to two seasons and an observation period before and after each launch. Some effects of the intervention may only become apparent after a longer period of time and will thus be missed due to the limited duration of the observation.

In sum, this study will add further knowledge to theory-based and evidence-informed development of interventions based on the assessment of relevant behavioural determinants within the target group. Lessons learned from this project can have an additional positive impact on campaign development especially for the growing 60+ age group for various other health behaviours (e.g., healthy diets, physical activity, age-related prevention campaigns such as screenings). The study uses a sophisticated and multi-faceted approach to evaluation, which can identify chances and pitfalls of several data sources. It could therefore serve as a benchmark for future evaluation studies.

## Abbreviations

AOK PLUS: Die Gesundheitskasse für Sachsen und Thüringen (a statutory health insurance in Thuringia and Saxony)
ASHIP: Association of Statutory Health Insurance Physicians
IPD: invasive pneumococcal disease
SAGE: Strategic Advisory Group of Experts on Immunization
SQG: Multidisciplinary Quality Assurance in the Healthcare System
STIKO: German Standing Committee on Vaccinations
UCD: User Centred Design
WHO: World Health Organization
